## Abstract

**Background::**

Orofacial pain encompasses painful conditions, such as temporomandibular disorder (TMD). Multidisciplinary health teams seek to control such musculoskeletal disorders to improve the quality and functional capacity of the muscles of mastication. The aim of the proposed study is to evaluate the effect of low-level laser therapy as a form of treatment for the prevention of initial fatigue of the muscles of mastication (masseter and anterior temporal muscles) as well as the recovery of these muscles after induced exhaustion (caused by isometric contraction) in young adults.

**Methods::**

The participants will be 78 healthy male and female volunteers between 18 and 34 years of age. The volunteers will be randomly allocated to a laser group (n = 26), sham group (n = 26), and control group (n = 26). All participants will be submitted to a clinical evaluation to record mandibular movements, bite force, muscle sensitivity to palpation, and initial muscle fatigue. Initial fatigue will be induced by isometric contraction of the jaws. Maximum voluntary contraction will be performed to record the time until initial exhaustion of the masseter muscle (determined by electromyography). The groups will then be submitted to the interventions: active laser therapy (wavelength: 780 nm; fluence: 134 J/cm^2^; power: 50 mW; irradiance: 1.675 W/cm^2^; exposure time: 80 seconds per point) on 3 points of the masseter and 1 point on the anterior temporal muscles on each side; sham laser (placebo effect); or no intervention (control). Maximum voluntary contraction will be performed again after the interventions to record the time until initial exhaustion of the masseter muscle (determined by electromyography). Differences in individual time until exhaustion between the pre- and postintervention evaluations will be measured to determine the effect of low-level laser therapy.

**Discussion::**

Although studies have been made with the use of low-level laser therapy in TMDs and on the effect of photobiomodulation on fatigue, this the first study to test this therapy in the prevention of fatigue in this region. The clinical relevance lies in the fact that longer dental procedures could take place if the patients are less prone to fatigue.

## Introduction

1

Orofacial pain encompasses painful conditions of the mouth and face, such as temporomandibular disorder (TMD), which is defined as a set of painful or dysfunctional conditions that involve the muscles of mastication and the temporomandibular joint (TMJ).^[1]^ The masseter muscle has been found to be more susceptible to fatigue in certain adverse health conditions, such as TMD, chronic headache and neck injuries in some studies but is reported to be unaffected in other studies.^[2]^

Low-level laser therapy has been increasingly administered in recent years in an attempt to delay the process of muscle fatigue and improve muscle performance. Experiments performed with animals using red (655 nm) and infrared (904 nm) wavelengths demonstrate positive results in the improvement of muscle performance and studies involving human subjects report improvements with regard to strength training and recovery from exhaustion.^[3]^ Biostimulation with low-level laser is reported to have a set of positive effects, such as the acceleration of the healing of bone defects in vivo and in vitro, the stimulation of blood flow, the recruitment and activation of osteoblasts, the promotion of osteosynthesis, and a reduction in osteoclast activity as well as anti-inflammatory action.^[1,4]^

Surface electromyography (EMG) is used in the study of bioelectrical phenomena that occur in skeletal muscle fibers at rest as well as during effort and maximum contraction.^[5]^ EMG is a noninvasive technique that is easy to execute and enables the determination of the electrophysiologic behavior of muscles in different physiologic conditions. It can therefore assist in the detection of muscle fatigue. Surface EMG has been widely used by physicians, speech therapists, physiotherapists, and physical educators for the study of human movement.^[6]^ EMG clearly confirms and can quantify the presence and severity of muscular electrical dysfunction. Levels of EMG activity demonstrate the extent to which muscles are electrically active. Surface EMG is used in clinical practice, research, sports science, and other distinct fields. The use of EMG together with other clinical methods enables a better understanding of the electroneurophysiologic action of muscles.

The aim of the proposed study is to evaluate the effects of phototherapy on the muscles of mastication, on bite force, the range of mandibular movements, sensitivity to palpation, and time to exhaustion of the masseter and anterior temporal muscles when administered prior to the induction of muscle fatigue.

## Materials and methods

2

### Type of study

2.1

A randomized, blind, clinical trial will be conducted with both placebo and control groups. The guidelines for research involving human subjects stipulated in Resolution 466/2012 of the Brazilian National Board of Health will be followed and the study has been approved by the Human Research Ethics Committee of University Nove de Julho, under process number 76402417.2.0000.5511. The participants will sign a statement of informed consent after receiving clarifications regarding the objectives and procedures of the study.

The protocol is in accordance with the 2013 SPIRIT (Standard Protocol Items: Recommendations for Interventional Trials) Statement. The SPIRIT checklist can be found as an additional file and Figure 1 is the SPIRIT figure. SPIRIT was developed to provide guidance in the form of a checklist of recommended items to include in a clinical trial protocol, to help improve its content and quality.

**Figure 1 F1:**
[figure not shown]
Standard Protocol Items: Recommendations for Interventional Trials (SPIRIT) figure as recommended by 2013 SPIRIT statement.

### Trial registration

2.2

Clinicaltrials.gov as NCT03460639, first posted March 9, 2018; https://clinicaltrials.gov/ct2/show/record/NCT03460639

### Sample calculation

2.3

The G∗ Power software (v.3.1.9.2, Franz Faul, Universität Kiel, Germany) was used for the calculation of the sample size, considering 3 groups (active laser, sham laser, and control) that will be evaluated before and after the interventions. To detect mean differences, 26 volunteers will be needed for each group (total: 78 volunteers).

Inclusion criteria: age 18 to 34 years, absence of TMD, and signed statement of informed consent.

Exclusion criteria: currently undergoing orthodontic or orthopedic treatment of the jaws, psychologic treatment or physical therapy, currently taking muscle relaxant or anti-inflammatory agent or using a bite plate.

### Recruitment and randomization

2.4

Healthy male and female young adults enrolled at University Nove de Julho (Vergueiro campus) in São Paulo will be evaluated (Fig. 2). Since they will already be on campus, the process of recruitment will be simple. Patients will be divided by block randomization into the groups.

**Figure 2 F2:**
[figure not shown]
Flowchart activity.

## Outcomes

3

### Induction of fatigue and EMG

3.1

The volunteer will be seated on a chair with back supported, eyes open, feet parallel on a rubber mat, and hands resting on thighs. The examination will be performed under 2 conditions: in normal postural position with mandible at rest; during maximum voluntary contraction (MVC) with Parafilm M placed between the teeth.

In the resting position, the volunteer will remain with the jaw relaxed, the teeth separated and the lips in contact for 15 seconds. For MVC, the volunteer will be instructed to place a Parafilm M between the maxillary and mandibular premolars and second molars bilaterally and perform isometric contraction for 45 seconds after a verbal command.

A contraction protocol will be used to induce fatigue.^[7]^ MVC clenching the teeth will be performed to record the time until initial exhaustion of the masseter muscle (determined by EMG). The groups will then be submitted to the interventions and MVC will be performed a second time to record the time until initial exhaustion of the masseter muscle (determined by EMG). During the procedures, the volunteers will receive verbal encouragement as well as visual feedback on the monitor to maintain MVC. Before the readings, the volunteers will undergo training of the procedure for the acquisition of the EMG signal.^[8]^

### Laser application protocol

3.2

Photobiomodulation will be performed with the Twin Flex Evolution device from MM Optics (São Carlos, SP, Brazil). The protocol proposed by Godoy et al^[9]^ for the control of facial muscle pain will be employed. This protocol was used in a previous study and proved effective when 12 consecutive applications were performed with the aim of evaluating the immediate effect of irradiation.^[4]^

The volunteer will be seated in a quiet environment without sound interference and positioned with the Frankfurt plane parallel to the floor. The active tip of the laser will be covered with plastic wrap to avoid cross-contamination and for reasons of hygiene. The sites to be irradiated will first be cleaned with 70% alcohol.

Three points on the masseter muscle (upper, middle, and lower portions) and 1 point on the anterior temporal on each side of the face will be irradiated with a wavelength of 780 nm, radiant exposure of 134 J/cm^2^, power of 50 mW and irradiance of 1.675 W/cm^2^ for 80 seconds per point, resulting in an energy of 4 J per point and total energy of 32 J per volunteer.^[4,9]^ Point application will be performed with a conventional tip in contact with the skin (beam spot: 0.04 cm^2^). All parameters can be found in Table 1.

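### The beam spot stated in section 3.2 is incompatible with its own irradiance and radiant exposure, so the laser dose per unit area is not fixed, although the energy dose is

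*Protocol article*

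**What the plan says.** Section 3.2 of the protocol article describes irradiation at 780 nm of three masseter points and one anterior temporal point on each side of the face, eight points in all. For each point it gives a "radiant exposure of 134 J/cm^2^, power of 50 mW and irradiance of 1.675 W/cm^2^ for 80 seconds per point". It then states the energy that follows, "resulting in an energy of 4 J per point and total energy of 32 J per volunteer". The next sentence describes application "with a conventional tip in contact with the skin (beam spot: 0.04 cm^2" (the unit is square centimetres).

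The Methods paragraph of the abstract repeats four of these values, "fluence: 134 J/cm^2^; power: 50 mW; irradiance: 1.675 W/cm^2^; exposure time: 80 seconds per point", without a spot area. Section 3.2 refers to Table 1 for the full set of parameters; the content of that table is not visible in the text at hand.

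**The concern.** Irradiance is power divided by spot area, and radiant exposure is energy divided by spot area. Once power, time and area are stated, both per-area values are determined and cannot be chosen separately. Section 3.2 states all five quantities, and the two per-area values do not follow from the other three.

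Active irradiation is what separates the laser group from the sham group, in which the same procedures are carried out with the device switched off. The article chose to describe the treatment per unit area, in both the abstract and section 3.2. If those values are in doubt, a positive or a null result cannot be tied to a known irradiance and fluence, and another group cannot repeat the treatment at the same per-area dose.

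**Working it through.** **Inputs, all from section 3.2**

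- Power P = 50 mW = 0.050 W
- Time per point t = 80 s
- Spot area A = 0.04 cm²
- Stated irradiance 1.675 W/cm²
- Stated radiant exposure 134 J/cm²
- Stated energy 4 J per point and 32 J per volunteer
- Points: (3 + 1) per side × 2 sides = 8

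**Step 1. Figures that reproduce**

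- Energy per point = P × t = 0.050 × 80 = 4 J, as stated.
- Total energy = 8 × 4 = 32 J, as stated.
- Radiant exposure = irradiance × time = 1.675 × 80 = 134 J/cm², so the two per-area figures agree with each other.

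**Step 2. Figures that do not reproduce**

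| Quantity | Formula | From stated P, t and A | Stated | Ratio |
|---|---|---|---|---|
| Irradiance | P / A | 0.050 / 0.04 = 1.25 W/cm² | 1.675 W/cm² | 1.34 |
| Radiant exposure | P × t / A | 4 / 0.04 = 100 J/cm² | 134 J/cm² | 1.34 |

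Both stated values are 34% above what the stated power, time and spot give. The common ratio points to a single mismatch between the area and the per-area pair, not to two separate slips.

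**Step 3. Could rounding explain it?**

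- Areas that round to 0.04 cm² run from 0.035 to 0.045 cm². At 50 mW these give 0.050 / 0.035 = 1.43 down to 0.050 / 0.045 = 1.11 W/cm², and 4 / 0.035 = 114 down to 4 / 0.045 = 89 J/cm².
- Taking power as high as 55 mW together with the smallest such area gives 0.055 / 0.035 = 1.57 W/cm² and 0.055 × 80 / 0.035 = 126 J/cm².

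Both remain short of 1.675 and 134, so rounding does not explain the gap.

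**Step 4. What area would the stated per-area values need?**

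- From irradiance: 0.050 / 1.675 = 0.0299 cm².
- From radiant exposure: 4 / 134 = 0.0299 cm².

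Both give about 0.030 cm², which does not round to 0.04. This shows where the conflict lies; it does not show which figure is wrong.

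**The case against.** The strongest reply is that the treatment can be carried out as written. Section 3.2 names the device, wavelength, power, time per point, contact technique, type of tip, and the number and sites of the points. Power, time, energy per point and total energy agree exactly. With one device, one tip and fixed settings, a misreported area or per-area value does not change what each volunteer receives. The comparison between groups, the sample size and the analysis are untouched. This all stands, and it limits the point to the dose per unit area.

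A reader might infer more than the documents support, in four ways:

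- **That the dose as a whole is undefined, or that an operator could not deliver the protocol.** The energy dose is defined, and 50 mW for 80 s at eight points can be delivered. Only the complete set of stated values cannot hold together.
- **That the total energy is in doubt.** Keeping both 0.04 cm² and 1.675 W/cm² would require 1.675 × 0.04 = 0.067 W, that is 67 mW, with 0.067 × 80 = 5.36 J per point and 8 × 5.36 = 42.9 J per volunteer. That contradicts three stated figures that agree with each other (50 mW, 4 J and 32 J). The documents do not exclude it, but nothing in them supports it.
- **That the treatment departs from the earlier protocol cited as effective.** The cited sources are not at hand, so this cannot be assessed.
- **That Table 1 or the abstract is wrong in itself.** Table 1 cannot be seen. The abstract gives no spot area and is consistent on its own terms. The contradiction arises within section 3.2, and the abstract is involved only because it repeats the same irradiance and radiant exposure.

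**Conclusion.** The point holds for the dose per unit area. With the stated power, time and spot, irradiance is 1.25 W/cm² and radiant exposure 100 J/cm², against the stated 1.675 W/cm² and 134 J/cm². The stated values are 34% higher, beyond what rounding of the spot area allows, even with 55 mW taken for the power. The energy dose of 4 J per point and 32 J in total is consistent.

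The calculation assumes only that the three per-point quantities carry their usual definitions: irradiance as power over area, radiant exposure as energy over area, energy as power times time. It needs no outside figure. The harm is to interpretation and replication at a known irradiance and fluence, not to the validity of the group comparison. It still needs correcting, because these values define the experimental treatment. The documents do not show which figure is in error, and none is recommended here.

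**What to change.** Before treatment starts:

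1. Measure the output power and confirm the spot area of the tip that will actually be used.
2. Recompute irradiance (power / area) and radiant exposure (power × time / area) from those two values and the exposure time.
3. Reconcile the figures in section 3.2 and the abstract, and check that Table 1 agrees with them.

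The cost is one check of the existing device and tip, and corrected text wherever a figure proves wrong. The design, sample size and analysis do not change. The sponsor must settle which values are correct.

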**Table 1 T1:**
[figure not shown]
Laser parameters.

The same procedures will be performed in the sham group, but the device will be switched off and a recording of the emission sounds will be used to give the volunteer the auditory sensation of laser therapy.

### Research diagnostic criteria for TMD

3.3

The research diagnostic criteria for temporomandibular disorder (RDC-TMD) questionnaires will be filled out by the volunteers for the diagnostic investigation of TMD. A specific clinical examination will be performed always by the same previously trained evaluator and will consist of palpation of the trapezius, sternocleidomastoid, temporal, masseter, digastrics and medial pterygoid muscles, palpation of the TMJs, analysis of mandibular movements (vertical and horizontal movements measured with digital calipers), the verification of joint sounds and the investigation of frequent headaches, facial pain, fatigue and difficulty chewing, bruxism, psychologic aspects, and parafunctional habits. Volunteers classified in groups I, II, or III of the RDC-TMD will be excluded from the study.

### Bite force

3.4

The DMD digital dynamometer (Kratos Equipamentos Industriais Ltda, Cotia, SP, Brazil) will be used to measure bite force. This is an electronic device composed of a bite fork and digital display connected by a wire. Readings will be taken with the fork in the region of the first molars and the data will be recorded in kilograms of force. The participants will receive instructions and training prior to the readings. Six readings will be made (3 on each side), alternating sides between readings. Each reading will last 5 seconds, with a 1-minute rest between readings.^[10]^ Bite force will be measured before and after the interventions.

### Range of mandibular movements

3.5

For the evaluation of the range of mandibular movements, we will follow the guidelines of the International Association for Dental Research for the use of the RDC-TMD, with a single measurement of each movement.^[11]^ The volunteer will be instructed to open his/her mouth as wide as possible for the measurement of maximum voluntary vertical mandibular movement with the aid of digital calipers (distance between maxillary and mandibular central incisors). The volunteer will then repeat the movement and the calipers will exert pressure against the maxillary and mandibular incisors to obtain maximum passive vertical mandibular movement. These procedures will be performed at the initial and final evaluations to record the range of mandibular movements before and after the interventions.

### Pain evaluation

3.6

The visual analog scale will be used to record pain upon palpation of the masseter and anterior temporal muscles. This is a numeric scale that ranges from 0 (absence of pain) to 10 (most intense pain).^[12]^ The scale will be used at the initial and final evaluations to record pain before and after the interventions.

### Statistical analysis

3.7

The results will be submitted to statistical analysis. The Shapiro–Wilk test will be used to determine adherence to the Gaussian curve. Parametric data will be compared using repeated-measures analysis of variance and nonparametric data will be compared using the Kruskal–Wallis test. A *P* < .05 will be considered indicative of statistical significance.

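### For outcomes measured once before and once after the intervention, baseline-adjusted ANCOVA would be more precise than the planned repeated-measures ANOVA, at almost no cost

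*Protocol article*

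**What the plan says.** Section 3.7 (Statistical analysis) of the protocol article fixes the method: "Parametric data will be compared using repeated-measures analysis of variance". Kruskal-Wallis is the route for non-normal data, and a P value below .05 "will be considered indicative of statistical significance". The section names neither the term of the ANOVA that carries the treatment effect nor a baseline covariate.

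The design has two time points. Section 2.3 describes the sample size as "considering 3 groups (active laser, sham laser, and control) that will be evaluated before and after the interventions", and section 2.4 says that the groups are formed by block randomisation. For time to exhaustion, section 3.1 has one contraction recorded first, after which "The groups will then be submitted to the interventions and MVC will be performed a second time". Section 3.4 adds "Bite force will be measured before and after the interventions", and sections 3.5 and 3.6 do the same for mandibular range and pain.

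The abstract (Methods) states the effect measure for one outcome only: "Differences in individual time until exhaustion between the pre- and postintervention evaluations will be measured to determine the effect of low-level laser therapy".

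**The concern.** In a two-time-point repeated-measures ANOVA, two terms involve the arm, and each uses the baseline less well than a regression adjustment.

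- **Group-by-time.** This term is the comparison of pre-to-post change between arms. It subtracts the whole baseline value, so it fixes the slope of post on pre at 1. When the true slope is below 1, that over-corrects and adds noise.
- **Group main effect.** This term compares the average of the pre and post values. The intervention cannot have altered the pre value, so the average carries only half of the treatment difference.

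ANCOVA estimates the slope from the data. What is at stake is precision and power from the same 78 volunteers, using a baseline that is already measured. A second, conditional risk is that someone reports the group term as the treatment effect because section 3.7 does not say which term to read.

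**Working it through.** **The plan's own figure.** Section 2.3 states "26 volunteers will be needed for each group (total: 78 volunteers" but gives no effect size, SD, power or correlation, so 78 cannot be reproduced. Unrelated inputs reach it. With 3 groups and 2 time points, a between-groups test with f = 0.40, 95% power and r = 0.5 gives 78. An interaction test with f = 0.15, 85% power and r = 0.7 also gives 78. The stated size therefore neither confirms nor rules out an allowance for the loss described here.

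**Inputs from the article.** Three randomised arms of 26, one pre and one post value, significance level .05.

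**Assumptions, because the article gives no figure.** The laser arm is 0.7 SD better than both other arms after the intervention, sham equals control, pre and post SDs are equal (set to 1), data are normal, and the pre-post correlation r lies between 0.3 and 0.9.

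**Step 1: the interaction is the change-score test.** In one simulated data set of 3 × 26, the group-by-time F and the one-way ANOVA F on change scores were both 5.55195.

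**Step 2: variance per person, on the scale of the post-intervention difference d.**
- Group term: it targets d/2 with variance (1 + r)/2. Rescaling to d multiplies the variance by 4, giving 2(1 + r).
- Interaction (change score): 2(1 − r).
- ANCOVA: 1 − r² = (1 − r)(1 + r).

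The ratio of ANCOVA to change score is (1 − r)(1 + r) / [2(1 − r)] = (1 + r)/2. The ratio of group term to ANCOVA is 2/(1 − r), for example 4.0 at r = 0.5.

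**Step 3: power of the three-arm F test.** The noncentrality is λ = 26 × (2/3) × 0.7² / variance = 8.493 / variance. The factor 2/3 is the sum of squared deviations of the arm means (0, 0, 1) from their average. Error df are 75 for the two ANOVA terms and 74 for ANCOVA. At r = 0.5 the variances are 3.0, 1.0 and 0.75, so λ = 2.83, 8.49 and 11.32.

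| r | (1 + r)/2 | Variance saved by ANCOVA | Power: group term | Power: interaction | Power: ANCOVA |
|---|---|---|---|---|---|
| 0.3 | 0.65 | 35% | 34% | 57% | 77% |
| 0.5 | 0.75 | 25% | 30% | 73% | 85% |
| 0.7 | 0.85 | 15% | 26% | 92% | 96% |
| 0.8 | 0.90 | 10% | 25% | 99% | 99% |
| 0.9 | 0.95 | 5% | 24% | ~100% | ~100% |

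In terms of volunteers, 78 × (1 + r)/2 gives about 51, 58, 66, 70 and 74. ANCOVA on those totals matches the change-score test on 78.

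**Step 4: unequal SDs.** Change-score variance minus ANCOVA variance equals (SD_pre − r × SD_post)². It is never negative, and it is zero when the slope r × SD_post / SD_pre equals 1. With an SD ratio (post/pre) of 1.3 and r = 0.8 the slope is 1.04 and the variance ratio is only 1.003.

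**Step 5: simulation check.** Over 4,000 runs per setting with no treatment effect, all three tests rejected in about 5% of runs (4.5 to 5.6%). With d = 0.8 and r = 0.5, simulated power was 37, 84 and 93% for group term, interaction and ANCOVA, equal to the formula values. The ANCOVA slope was estimated in these runs, so the cost of estimating it is included.

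**The case against.** The strongest reply is that the abstract already ties the laser effect to individual pre-to-post differences in time until exhaustion. With two time points that is the group-by-time term, an unbiased test under randomisation that holds its type I error. A condensed article may leave the naming of the term to a fuller analysis plan. The loss also depends wholly on a correlation the article does not give. The same person repeats the same task around an intervention, and bite force rests on six readings, so a high correlation is possible; at r = 0.8 or above the power difference is negligible in this scenario.

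Most of this stands, and it rules out three stronger readings:

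- A reader might infer that the trial will test the group main effect and so probably miss a real laser effect. The documents do not support that. The abstract points to the interaction for time until exhaustion, and the 24 to 34% power applies only if the group term is read. The abstract is silent on the term for bite force, range and pain, so the ambiguity is real but limited.
- A reader might infer that the baseline is thrown away. The interaction uses it, with the slope fixed at 1.
- A reader might infer that the analysis is invalid. It is not.

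The gains are normal-theory results and may not carry over to the 0 to 10 pain score, where floor values are plausible in volunteers without TMD, or to anything sent to Kruskal-Wallis. Nor do the documents show skewness in time to exhaustion, so they give no ground for prescribing a transformation.

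The reply does not remove the main point. Low and moderate correlations cannot be excluded either, and ANCOVA costs almost nothing whichever holds.

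**Conclusion.** The point holds as one of efficiency. For outcomes analysed parametrically, section 3.7 commits to a method whose relevant term is valid but never more precise than ANCOVA, apart from one error degree of freedom.

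The size depends on the unstated correlation. The gain is material at r of 0.3 to 0.5 (20 and 12 percentage points of power in the assumed 0.7 SD scenario), small at 0.7 (about 4 points) and negligible at 0.8 to 0.9. With unequal SDs it disappears when the slope of post on pre is 1. The ordering of the methods is algebra; the power figures rest on the assumed effect, equal SDs and normality. The unnamed term adds a conditional risk, which naming the treatment contrast removes.

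**What to change.** In section 3.7, for outcomes analysed parametrically, replace repeated-measures ANOVA with ANCOVA: post-intervention value as outcome, arm as factor, and the pre-intervention value of the same outcome as covariate. State that the treatment effect is the adjusted laser-sham difference, reported with its 95% confidence interval. This also settles which term is to be read.

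The cost is one sentence and one error degree of freedom (74 in place of 75). No further measurement, visit or volunteer is needed, because the baseline values are already collected.

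### A normality test switches the analysis to a Kruskal-Wallis test with no stated variable; one baseline-adjusted analysis would keep the question fixed and generally gain power

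*Protocol article*

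**What the plan says.** Three places in the protocol article bear on this.

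- **Section 3.7, Statistical analysis.** "The Shapiro–Wilk test will be used to determine adherence to the Gaussian curve". Depending on the result, "Parametric data will be compared using repeated-measures analysis of variance" or "nonparametric data will be compared using the Kruskal–Wallis test". Neither clause names the variable analysed, and the section does not say whether normality is checked on raw values, changes or residuals.
- **Abstract, Methods.** The effect measure is one number per person: "Differences in individual time until exhaustion between the pre- and postintervention evaluations will be measured to determine the effect of low-level laser therapy".
- **Section 2.3, Sample calculation.** The design is sized "considering 3 groups (active laser, sham laser, and control) that will be evaluated before and after the interventions", with 26 volunteers in each arm.

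Sections 3.4 to 3.6 also record bite force, range of mandibular movement and palpation pain before and after the interventions. They define no change score for these outcomes.

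**The concern.** The two branches of section 3.7 are not obviously answers to the same question. Repeated-measures ANOVA takes both measurements from each person, and its group-by-time term asks whether change differs between arms. Kruskal-Wallis takes one value per person from independent groups. It has no pairing and no time factor.

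If the fallback is run on post-intervention values, baseline is discarded and the pre-to-post difference named in the abstract is not what is tested. If it is run on change, the question is preserved. The text leaves both open, so a P value from a normality test, together with a later choice of variable, could settle what is tested on the outcome that determines the laser effect.

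At stake are a question fixed before the data are seen, and power. Baseline readings are collected on everyone, and a method that ignores them leaves stable between-person differences in clenching endurance in the error term.

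**Working it through.** **Inputs from the article.** Three arms, 26 per arm, 78 in total, two time points, significance at P < .05.

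**The article's own figure.** The total of 78 cannot be reproduced, because section 2.3 gives no effect size, SD, pre-post correlation or power. Everything below therefore rests on assumptions.

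**Step 1: is Kruskal-Wallis on change a legitimate counterpart?** With two time points, the group-by-time F from repeated-measures ANOVA equals the one-way ANOVA F on post minus pre. A numerical check on simulated data for 3 × 26 participants gave F = 1.8048 both ways. Kruskal-Wallis on change is the rank version of that one-way test, so it addresses the question in the abstract.

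**Step 2: why the choice of variable matters.** Let σ² be the variance at each time point and r the pre-post correlation. The error variances are:

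- post values: σ²
- change: 2(1 − r)σ²
- baseline-adjusted (ANCOVA): (1 − r²)σ²

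| r | post | change | ANCOVA |
|---|---|---|---|
| 0.3 | 1.00 | 1.40 | 0.91 |
| 0.5 | 1.00 | 1.00 | 0.75 |
| 0.7 | 1.00 | 0.60 | 0.51 |
| 0.8 | 1.00 | 0.40 | 0.36 |

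(multiples of σ²)

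Change beats post values only when 2(1 − r) < 1, that is, when r > 0.5. For any r strictly between 0 and 1, the ANCOVA variance is below both: 1 − r² < 1, and 1 − r² = (1 − r)(1 + r) < 2(1 − r).

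**Step 3: power by simulation.** Assumptions: log times are bivariate normal with SD 0.5; the laser arm is shifted by 0.7 SD on the log scale at the post reading; sham and control are equal; 2,000 runs per cell; test at 0.05.

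| Method | r = 0.3 | r = 0.5 | r = 0.7 | r = 0.8 |
|---|---|---|---|---|
| Kruskal-Wallis, post values | 71% | 69% | 69% | 69% |
| Kruskal-Wallis, change | 58% | 71% | 90% | 98% |
| Rank ANCOVA | 74% | 80% | 93% | 98% |
| ANCOVA on log time | 76% | 84% | 96% | 99% |

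With no effect, all four methods rejected in 4-6% of runs. A repeat with a different random seed agreed to within about 3 percentage points in every cell.

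**Step 4: check against a formula.** For normal data with arm means 0.7, 0 and 0 in SD units, f² = 0.7² × 2/9 = 0.109. The noncentrality on post values is then 78 × 0.109 = 8.49. The noncentral F gives 73% power for ANOVA on post values. Dividing 8.49 by the multipliers in Step 2 gives 57 / 73 / 92 / 99% for change and 77 / 85 / 96 / 99% for ANCOVA. The simulation follows this pattern, with the rank methods slightly lower in most cells.

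**The case against.** The strongest reply is that the abstract already supplies the variable. Individual differences in time to exhaustion are one independent value per participant in three groups, which is what Kruskal-Wallis handles. On that reading the switch does not change the question, because the fallback is the rank version of the group-by-time test. This stands. A reader might infer from section 3.7 that Kruskal-Wallis cannot test the pre-to-post difference at all; the article does not support that, because nothing in it says that raw or pooled values will be used. The reply covers only time to exhaustion, however. No change score is defined for bite force, mandibular range or pain.

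A second reply is that post values may properly be compared between randomised arms. That also stands: type I error held in every cell, so an inference that the plan inflates false positives would be wrong.

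A third is that the switch may never fire. The article gives no outcome distributions, so its likelihood cannot be derived. It does depend on how the gate is applied: tested at 5% in each of six independent group-by-time cells, exactly normal data would fail at least once with probability 1 − 0.95⁶ = 26%.

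A fourth is that an analysis plan not shown may name the variable. It may, and the omission alone would not be a finding. What the article does fix is the normality gate and the pairing of these two tests, and a better method is available from data already being collected.

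**Conclusion.** The concern holds in a limited form. Section 3.7 makes the analysis depend on a normality test and falls back on a method that tests the abstract's effect measure only if it is applied to individual change, which the section does not say.

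The size depends on the unknown pre-post correlation. Under the assumptions above, Kruskal-Wallis on post values falls short of ANCOVA on log time by 5 percentage points at r = 0.3 (71% against 76%) and by 30 at r = 0.8 (69% against 99%). Kruskal-Wallis on change falls short by 18 points at r = 0.3 (58% against 76%) and by 1 at r = 0.8. Rank ANCOVA was at least as powerful as either Kruskal-Wallis version at every r, with a tie at 98% against change at r = 0.8.

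The 0.7 SD shift, the log-normal shape and the range of r are assumptions, not figures from the article. The ordering of ANCOVA over post values and change follows from the variances in Step 2 and does not depend on the size of the shift. Severity: should-fix.

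**What to change.** Replace the normality-gated switch in section 3.7, or in the analysis plan, with one prespecified baseline-adjusted analysis per outcome. For time to exhaustion, use ANCOVA on log time with arm as factor and baseline log time as covariate, and name rank ANCOVA as the robust version. Name one baseline-adjusted analysis each for bite force, mandibular range and palpation pain. Use Shapiro-Wilk only as a diagnostic on model residuals, with no power to change the test.

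At minimum, if Kruskal-Wallis is kept, state that it is applied to each participant's post-minus-pre change for every outcome. Record that this can have less power than post values when the pre-post correlation is below about 0.5, which is why baseline adjustment is the better repair.

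The cost is a few sentences, with no new measurements and no change to the 78 participants. The choice should be recorded before outcome data by arm are seen.
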